### Duration of treatment in the trial

The intervention is transfusion of any allogenic blood product between the start of surgery and 48 h postoperatively.

### End of the trial

For an individual participant, the end of the trial is defined as completion of the 3-month postal follow-up assessment.

### Clinical management of study participants

#### Administration of non-RBC blood components

Patients receiving LVBT frequently receive non-RBC components. These will be administered according to standard unit protocols, with the indication, volume and timing of their administration recorded. Platelet transfusions will not be washed in this study.

#### Blood management adjuncts

A single cell salvage device will be used for allogenic and autologous red cell washing and transfusion. Intraoperative cell salvage will be used in every patient with washing, resuspension in normal saline and autotransfusion as per standard care. Cardiotomy suction will be returned directly to the extracorporeal circuity without washing. Postoperative salvage of mediastinal fluid will not be performed. Tranexamic acid will be administered to every patient as per the BART (Blood Conservation Using Antifibrinolytics in a Randomized Trial) protocol.^42^ In patients refractory to two standard doses of non-RBC blood components (a standard dose=1 pooled adult platelets and 2–4 units of fresh frozen plasma, 2 units of cryoprecipitate), recombinant activated factor VII or prothrombin complex concentrate, may be administered at the discretion of the attending clinician.

#### Concomitant treatment

Patients may receive medications and/or other therapies to treat adverse events as deemed necessary by the investigator or the patient's physician. Concomitant medications and/or therapy that become necessary during the study and any changes in concomitant medication and/or therapy will be recorded on the case report forms (CRFs). Details of concomitant medications and therapy will include generic drug name, dose, route, duration and indication.

#### Preoperative care

Eligible patients will receive standard care preoperatively.

#### Anaesthesia

A standard anaesthetic protocol will be used. Patients will undergo anaesthetic induction with midazolam/propofol/fentanyl (up to15 µg/kg) and short-acting muscle relaxant. Anaesthetic maintenance will use isoflurane/sevoflurane until start of cardiopulmonary bypass where propofol (1%, Diprivan, 20–40 mL/h) maintenance will be started until the end of the procedure. Target perfusion pressures (mean 70–80) will be maintained initially with incremental metaraminol or phenylephrine boluses (0.5 mg) or vasodilators, and post bypass with inotropic support as necessary. Morphine 10–15 mg and paracetamol 1 g are administered intravenously on chest closure to facilitate postoperative analgesia. Postoperative analgesia comprises regular paracetamol and morphine patient controlled analgesia (PCA) for up to 48 h where regular oral tramadol 50–100 mg is started. The anaesthetic agents will be recorded in the patient CRF.

#### Cardiopulmonary bypass

Cardiopulmonary bypass will be managed according to a standard CPB protocol. Normothermic to mild hypothermic non-pulsatile or pulsatile CPB (32–35°C) will be established using a standard venous reservoir, a roller pump, a hollow fibre oxygenator and a non-heparin-bonded circuit with target flows of 2.4–2.7 L/min/m^2^, and mean arterial blood pressure (MABP) maintained between 60 and 80 mm Hg. Circuit prime will typically include 1000 mL ringers lactate, 500 mL gelofusin, mannitol 20% and 5000 IU heparin. Intermittent antegrade/retrograde blood cardioplegic arrest will be performed. Hct will be maintained >23. Target-activated clotting time of >400 s will be achieved with heparin (300 µ/kg as a loading dose) for bypass. Heparin reversal will be achieved with the administration of protamine sulfate in a 1:1 ratio as per standard practice.

#### Postoperative care

Intravenous glycopyrolate, atropine, atrial or dual chamber epicardial pacing will be used to achieve a target heart rate (70–110 bpm). The use of inotropes or vasopressors will be at the discretion of the attending physician. Postoperative oliguria, defined as a urine output <0.5 mL/kg/h for four consecutive hours will be treated initially with fluid boluses to maintain the central filling pressure >12 mm Hg, and then inotropes (enoximone, dobutamine, epinephrine) or pressor agents (norepinephrine or vasopressin) as indicated to maintain adequate perfusion pressure (ie, MABP >80 mm Hg or within 10% of preoperative MABP), or cardiac output (ie, cardiac index >2.1 L/min/m^2^) as determined by appropriate invasive monitoring. Persistent oliguria resistant to these measures may be managed by forced diuresis, using, for example, furosemide. Decisions about discharge from ICU, high dependency unit (HDU) and from hospital will be made on the basis of existing institutional protocols.

### Research procedures

#### Screening and eligibility assessment

The patients risk score will be calculated at the preoperative assessment clinic or from our standard in patient referral protocols that include detailed clinical and demographic information (table 2). An information leaflet, approved by the local Research Ethics Committee, will be sent to all potentially eligible patients waiting at home with the letter giving a date for their operations. Each patient will have at least 24 h to consider whether to participate or not. In a few cases, this time interval may be as little as 12 h, for example, for patients admitted for urgent surgery without prior notification to the waiting list coordinator. Despite the short notice, it is important to include these patients for the applicability of the trial findings since about 40% of patients having cardiac surgery are admitted as urgent cases, and these are often those at greatest risk for LVBT. Written informed consent will be obtained at the time of admission. Details of all patients approached for the trial and reason(s) for non-participation (eg, reason for being ineligible or patient refusal) will be documented.

**Table 2 OPENHRT2015000344TB2:** Key data collection points

	Preoperation	Operation day	Day 1	Day 2	Day 3	Day 4	Discharge	6 weeks	3 months
Eligibility	✓								
Written consent	✓								
Randomisation	✓								
EQ5D Questionnaire	✓						✓	✓	✓*
Bloods: serum biochemistry (creatinine and troponin T/I)	✓†	✓† (CICU and 6–12 h)	✓† (24 h)	✓† (48 h)	✓† (72 h)	✓‡ (96 h)	✓‡		
Bloods: serum inflammatory biomarkers	✓†	✓† (CICU and 6–12 h)	✓† (24 h)	✓† (48 h)	✓† (72 h)	✓‡ (96 h)	✓‡		
Bloods: full blood counts	✓	✓ (CICU and 6–12 h)	✓ (24 h)	✓ (48 h)	✓ (72 h)	✓‡ (96 h)	✓‡		
Bloods: plasma sample for MP analysis and monocyte activation	✓	✓ (CICU)	✓ (24 h)	✓ (48 h)					
Urine sample and volume: NGAL, urea and elecrolytes	✓	✓ (6 and 12 h)	✓ (24 h)	✓†§ (48 h)					
Operative details		✓†							
Clinical outcomes						✓	✓	✓¶	
Serious adverse event monitoring		✓	✓	✓	✓	✓	✓	✓¶	
Resource use data							✓	✓¶	✓*
Bloods: platelet response**	✓**	✓** (CICU and 6–12 h)	✓** (24 h)	✓** (48 h)					

*Indicates data collection via postal questionnaire.

†Indicates samples taken as part of normal care.

‡Discharge time point if hospital stay exceeds 5 days.

§Indicates sample for determination of routine urea and electrolytes only.

¶The 4–6-week time point in accordance with normal postoperative care.

**Indicates Glenfield patients alone.

CICU, cardiac Intensive care unit; NGAL, neutrophil gelatinase-associated lipocalin.

#### Randomisation and code breaking

Patients will be randomly assigned in a 1:1 ratio using an internet-based randomisation system (Sealed Envelope Ltd, MHRA recognised facility). Randomisation will be stratified by: (1) study site; (2) type of procedure, coronary artery bypass grafts (CABG), valve, CABG and valve, other. Random allocations will be generated only after the relevant baseline data to identify the patient and the surgeon have been entered into the system, guaranteeing concealment of allocation and a definitive log of participants. Patients who consent will be randomised by a member of the research team at a participating site. If patients are unexpectedly rescheduled, they will retain their study numbers and randomised allocation.

Detailed instructions for the randomisation process will be provided in a separate manual (figure 3).

**Figure 3 OPENHRT2015000344F3:**
[figure not shown]
Patient flows showing randomisation, intervention period and follow-up period. Hct, haematocrit; RBC, red blood cell.

#### Trial-specific tests and procedures

Participants will undergo the following tests and procedures as part of the research.

*Urine samples* will be collected on the day before surgery, on the day of surgery (6 and 12 h postsurgery) and day 1 (24 h postsurgery) for the measurement of AKI biomarkers.

*Blood samples* will be collected from all participants in the trial at the following time points: preoperatively, postoperatively, on return to ITU, 6–12 h postoperative, 24 h postoperative, 48 h postoperative, 72 h postoperative, 96 h postoperative or hospital discharge, whichever is the earliest (ie, seven blood samples will be taken per patient). Inflammatory markers in serum; granulocyte-macrophage colony-stimulating factor (GM-CSF), interferon-γ, IL-1β, IL-2, IL-4, IL-5, IL-6, IL-8, IL-10 and tumour necrosis factor-α will be measured on the MagPix Multiplex platform (Luminex Corp). Preoperatively, on return to cardiac Intensive care unit (CICU) and 24 and 48 h postoperative, additional blood will be collected for analysis of MP levels and platelet and monocyte activation using flow cytometry (Beckman Coulter MCL-XK, High Wycombe, UK) and multiplate impedance electrode aggregometry (Roche, Rotkreuz, Switzerland).

Urine and blood samples will be transferred to the central laboratory where they will be stored until analysed for cytokines, coagulopathy, inflammatory cell activation, endothelial injury and inflammatory organ injury biomarkers. The samples will be kept until the completion of the study. Left over material may be used for future research with permission of the research participants. Full blood count analysis will be conducted at the local haematology laboratories of the participating sites.

*Assessment of cumulative resource use and utility* will be carried out for all participants: Utility will be assessed using the EuroQol EQ5D^39^ assessed at baseline, 6 weeks (routine clinic visit) and 3 months after surgery (postal questionnaire). Hospital resource use will be directly measured using available reference costs.^43^ Postdischarge resource use will be assessed using a health resource usage questionnaire conducted at 6 weeks (routine clinic visit) and 3 months after surgery (postal questionnaire) as previously described.^36^

#### Planned recruitment rate

On the basis of historical data, we estimate that there will be a target population of about 1300 (<25%) eligible from 5250 total patients over 18 months at all three centres (from the UK National Transfusion Audit and 2011–2012 activity.^11^ We plan to recruit 170, or 13% of all eligible patients lower than that regularly achieved in other trials carried out by these researchers.

#### Discontinuation/withdrawal of participants

Each participant has the right to withdraw at any time. It is unlikely for this trial that there would be any reason for the investigator to withdraw any participant, or for the participant to withdraw, from their allocated treatment arm as over 80% of all transfusions are administered within 24 h of surgery, when the majority of patients will remain sedated and/or ventilated. If a patient wishes to withdraw for any reason, we will continue to analyse any data already collected, unless the patient expresses a wish for their samples and any associated data to be destroyed. On the basis of an ongoing trial measuring similar end points (the PASPORT Trial ISRCTN23557269), we predict that data may be incomplete for approximately 10% of patients.

#### Measures taken to avoid bias

All necessary steps will be taken to reduce the risk of bias.^44^
^45^ The trial will be analysed on an intention-to-treat basis, that is, outcomes will be analysed according to the treatment allocation, irrespective of future management and events, and every effort will be made to include all randomised patients. Selection bias will be minimised by concealed randomised allocation. As the intervention utilises a large piece of bedside equipment, the autotransfusion device, it will be impossible to blind clinical staff and patients to the intervention. Detection bias will be minimised, however, by blinding of laboratory staff analysing cytokines, biomarkers and inflammatory processes. Specifically, urine and serum samples obtained exclusively for the trial will be identified only by a trial acronym, patient’ study ID, initials and date of birth, and the time at which the sample was taken, ensuring that laboratory staff performing analyses are blinded. Detection bias for the clinical outcomes will also be minimised by the use of objective outcome criteria; as defined in the Outcome section above. Staff recording components of the secondary outcome (any inflammatory injury, sepsis or death) at the time of discharge will be blinded to further minimise the risk of detection bias. Blood and other urine samples, that are also obtained as part of routine care will be analysed routinely in NHS laboratories by personnel who are unaware that the participant is in a trial. Decisions about discharge from ICU, HDU and from hospital will be made by clinical staff on the basis of existing institutional protocols. ICU/HDU transition will be defined as transition from level 3 (1:1 nursing ratio) to level 2 (1:2 nursing ratio). HDU/ward transition will be defined as time of arrival on the ward. In order to minimise attrition bias, we aim to include data for all randomised participants in the data analyses.

#### Adverse events

Serious and other adverse events are recorded and reported in accordance with the International Conference for Harmonisation of Good Clinical Practice (ICH GCP) guidelines and the Sponsor's (University of Leicester) Research Related Adverse Event Reporting Policy. University Hospitals of Coventry and Warwickshire Trust and Royal Victoria Hospital Blackpool will notify the trial team of all serious adverse events. Data on adverse events are collected from the time of surgery for the duration of the participant's postoperative hospital stay and for the 3-month follow-up period.

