#### Economic issues/analysis

Health economic analysis will be undertaken by the Health Economics Research Centre of the University of Oxford. Established guidelines will be followed for the economic evaluation.^47^ The main outcome measure will be quality-adjusted life years (QALYs), estimated using the EuroQol EQ5D.^39^ This questionnaire instrument will be administered face-to-face to patients at baseline and at 6 weeks. At 3 months postrandomisation, this questionnaire instrument will be administered via post to patients. Respondents will be assigned valuations derived from published UK population tariffs^48^ and the mean number of QALYs per trial arm and incremental QALYs will be calculated. Patients will be followed up for 6 weeks after surgery, at a routine outpatient clinic appointment and again at 3 months postrandomisation via postal questionnaire.

Data will be collected from the trial centres on healthcare resource use for transfusion, inpatient days by ward type, any complications and subsequent treatments for complications. Resource use will be measured in naturally occurring units; for example, staff time will be measured in terms of length of times for treatments and unit costs will be derived from nationally published sources.^43^ Bespoke questionnaires will be used at 6 weeks and 3 months postrandomisation to obtain estimates of healthcare resources used since hospital discharge, for example, readmissions to hospital and further contact with health professionals such as general practitioner visits.

Any missing outcome and cost data will be dealt with using multiple imputation methods. Our analysis will calculate the average cost and outcome on a per patient basis and from this the incremental cost-effectiveness ratios for the different trial arms will be derived, producing an incremental cost per QALY, or incremental cost per complication avoided. Probabilistic sensitivity analysis will be used to assess the impact on results of variation around key parameters such as costs for treatments for complications which will also assist with generalising the results to other UK settings. Results will be expressed in terms of a cost-effectiveness acceptability curve, which indicates the likelihood that the results fall below a given cost-effectiveness ceiling.

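### The text commits to adverse-event collection to 3 months, but Table 2 schedules serious adverse event monitoring only to 4–6 weeks

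*Protocol article*

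**What the plan says.** The Adverse events section gives the collection window in one sentence: it opens at surgery and covers the "postoperative hospital stay and for the 3-month follow-up period". It also requires the two centres outside Leicester to notify the trial team of every serious adverse event.

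Table 2 (key data collection points, under Screening and eligibility assessment) has a row headed "Serious adverse event monitoring". It is ticked for the operation day, days 1 to 4, discharge and 6 weeks. The 6-week tick carries this footnote: "The 4–6-week time point in accordance with normal postoperative care". The 3-month cell of the row is empty.

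Two rows of the table do have a 3-month tick, EQ5D and resource use. Both carry the footnote "Indicates data collection via postal questionnaire". The End of the trial section says that for an individual participant "the end of the trial is defined as completion of the 3-month postal follow-up assessment", so the weeks between the clinic visit and month 3 lie inside trial follow-up.

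**The concern.** Serious adverse events are a subset of adverse events, so the sentence in the text covers them to 3 months. The schedule does not. A centre that plans its contacts from Table 2 would make its last safety enquiry at the routine clinic visit. A centre that works from the text would go on to month 3. Nothing in the article says which governs.

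What is at stake is the safety record. If centres follow different parts of the document, ascertainment differs between them. If all follow the table, safety tabulations described as covering 3 months would have no scheduled enquiry behind more than half of that time. The monitoring committee receives outcome data by group every 6 months (Frequency of analysis) and would need to know which window applies. Spontaneous reporting is a weak substitute for a scheduled enquiry here, because clinical staff and patients know the allocation (Measures taken to avoid bias).

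Deaths are the sharpest case. The only 3-month contact described is a questionnaire posted to the patient, and a patient who has died cannot return it. Without a vital-status check, that silence looks like ordinary non-response.

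**Working it through.** There is no sample size, power or error rate to reproduce. The check is a cell-by-cell reading of Table 2 against the text, followed by the length of the unscheduled period.

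**1. The rows aligned with the column headings**

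| Row of Table 2 | Discharge | 6 weeks | 3 months |
|---|---|---|---|
| Serious adverse event monitoring | tick | tick (footnote: 4–6 weeks) | empty |
| Resource use data | tick | tick (footnote: 4–6 weeks) | tick (postal) |
| EQ5D questionnaire | tick | tick | tick (postal) |

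The 3-month column exists and is filled for other rows, so the empty cell is not explained by a column lost when the table was read from the PDF.

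**2. Length of the unscheduled period**

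Inputs: window stated in the text, surgery to 3 months; last scheduled safety contact, 4 to 6 weeks (Table 2 footnote). Both are counted from surgery.

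- 3 months in weeks: 365.25 / 4 / 7 = 13.04.
- Last contact at 6 weeks: 13.04 − 6 = 7.04 weeks; 7.04 / 13.04 = 54%.
- Last contact at 4 weeks: 13.04 − 4 = 9.04 weeks; 9.04 / 13.04 = 69%.

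**3. What could still pick up an event in those weeks**

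- The duty on the two other centres to notify serious adverse events. It is driven by events, is tied to no visit and has no stated cut-off. It works only if the centre hears of the event.
- The 3-month resource-use questionnaire. The Economic issues/analysis section says it covers readmissions and further contacts with health professionals. It would reveal readmissions among responders, but it is not described as adverse-event reporting and cannot be answered by a patient who has died.

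So some late events would surface and others may not. The documents give no rate of late events or late mortality, so the number that might be missed cannot be estimated from them.

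**The case against.** The strongest reply is that Table 2 lists key points only and is visibly not exhaustive. It has no row for postoperative transfusions, although the Red cells section requires every transfusion to be recorded. It has no day 5 column, although Table 1 asks for an organ dysfunction score on day 5. A blank cell therefore does not prove that nothing is collected, and the text does commit to 3 months. The routes in step 3 also remain open, and operational detail may sit in the full protocol. This stands to a point: the documents do not show that late events *are* missed, only that they may be. It does not remove the conflict. The table has a row for exactly this item, with a footnoted last contact and an empty cell beneath a column that other rows use.

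Two stronger readings are tempting, and neither is supported.

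- A reader might infer that the "Clinical outcomes" row, which also ends at the 6-week column, is a second contradiction. It is not. The 3-month commitment concerns adverse events, and no section promises clinical outcomes to 3 months. Measures taken to avoid bias has the composite that includes death recorded at discharge.
- A reader might infer that patients who die late would be imputed as survivors in the cost-effectiveness analysis, because "Any missing outcome and cost data will be dealt with using multiple imputation methods". That sentence does not class a death as missing data. How death enters the quality-adjusted life years is commonly left to an analysis plan, and none is shown here. No distortion of those estimates is claimed.

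**Conclusion.** The inconsistency is real and certain on the face of the article: adverse events to 3 months in the text, serious adverse event monitoring to 4–6 weeks in the schedule. It leaves about 7 to 9 of 13 weeks (54–69%) without a scheduled enquiry. The range depends only on when in the 4-to-6-week window the clinic visit falls, with 3 months taken as 13 weeks from surgery.

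The consequence is a risk of incomplete and uneven safety ascertainment after the clinic visit, deaths included. It is confined to safety reporting. Interleukin-8 is measured to 96 h and is untouched, and the Statistical analyses section already says that adverse events are too infrequent to compare between groups and will be tabulated. The point should be corrected because the correction is cheap and the stated window is wrong in one of the two places. It does not threaten the trial's main result.

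**What to change.** Make the Adverse events section and Table 2 agree.

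- **Preferred:** add a 3-month tick to the serious adverse event row and a 3-month vital-status entry. Collect serious events through the postal questionnaire already sent at that point. Establish vital status by a records check, ideally before the form is mailed. This keeps the window the text promises and separates death from non-response. It costs a table amendment, a line or two on an existing form and a small workload for site staff.
- **Alternative:** if 3-month collection is not intended, restate the window in the Adverse events section as ending at the 4–6-week visit, and label the monitoring reports and final safety tables accordingly. This costs only wording, but it gives up scheduled safety information for weeks in which participants are still in the trial.
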